#### Standard implementation strategy bundle

Build a Coalition: We will cultivate relationships with primary care and nursing leadership at each site, with the goal of increasing leadership awareness and buy-in for implementation efforts. To do so, the Implementation Team will facilitate meetings with site leaders to update them on implementation and elicit their feedback on project challenges to guide implementation efforts.Implementation Champions: One nurse and one PCP at each site will serve as Implementation Champions. Champions will help to facilitate problem-solving for the workflow of their site as it relates to implementing the intervention. Champions will receive monthly audit and feedback reports and will be responsible for sharing findings with other clinicians at their site.Local Technical Assistance: The Implementation Team will partner with clinicians, champions, and leadership to problem-solve issues related to implementation as they arise. Depending on site needs, additional technical assistance may include one-on-one meetings and weekly office hours to establish feedback channels to report on local progress and enhance buy-in and trust [48].System-level Audit and Feedback: Reports on Reach and proportion of patients with functional impairment at each site will be sent monthly by the Implementation Team to Clinical Champions and site leadership (e.g., medical center directors, nurse executives, PACT medical directors, nurse managers).

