#### Period 1 (Randomization to Standard or Enhanced Implementation; 3 months)

Our adaptive trial design will deploy resources to sites with the greatest need for enhanced implementation strategies [32–34]. After the Run-In period, data generated by the clinical screening tools (“Health Factors” data) will be used to identify sites with inadequate Reach, defined as < 80% of eligible veterans receiving LVN screening and/or PCP assessment (in keeping with standard benchmarks for adequate adherence to practice guidelines) [58]. We will define PCP assessment as reviewing LVN screening results and either (1) documenting via checkbox that further referral is not needed or (2) placing a referral to address identified impairments. We chose both LVN screening and PCP assessment as the benchmark for implementation response because these combined steps contribute to improved identification (via screening) and management (via assessment/referrals). Sites with ≥ 80% Reach at the end of the Run-In phase will receive the standard implementation bundle for all phases of implementation. For sites with < 80% Reach, we will randomize 1:1 by site to 3 additional months of standard vs. enhanced implementation. Based on current levels of functional status measurement in VA primary care practices (51% measuring function among ≥ 80% of eligible veterans), we anticipate that half of included sites (*n* = 4) will require enhanced implementation. The enhanced implementation strategy bundle will include the components of the standard bundle above (i.e., Coalition Building, Implementation Champions, Technical Assistance) plus clinician-level audit and feedback for participating LVNs and PCPs instead of site-level audit and feedback.

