### Outcome measures and sources by aim

#### Aim 1 (Implementation Outcomes)

The primary outcome for Aim 1 is Reach, with secondary outcomes of Adoption, Implementation (fidelity, adaptations), and Maintenance (Table 3). Reach is defined as the proportion of eligible Veterans who receive LVN screening and PCP assessment at each site. We will identify eligible veterans (i.e., ≥ 60 years old, seen in primary care after implementation begins) and use Health Factors to identify completed screening, defined as an LVN completing the electronic tool, and assessment, defined as a PCP reviewing screening results and either (a) documenting via checkbox that further referral is not needed or (b) placing a referral to address impairments.

Adoption is defined as the proportion of LVNs and PCPs at each site who regularly complete screening and assessment. Adequate adoption is defined as ≥ 80% [58]. To identify more nuanced aspects of adoption, we will review a randomly selected subset of charts at each site to examine if clinician notes for the visit when screening was completed have content related to functional status and type of content.

Fidelity to intervention core components will be assessed to determine if core components were implemented as intended, accounting for adaptations and modifications that were consistent vs. inconsistent with intent [48]. Study staff will complete fidelity checklists using electronic health record and qualitative data sources.

Recipient experience will be assessed using periodic reflections for champions, interviews for leadership, veterans, and family caregivers, and surveys for clinicians, and will be used to inform adaptations to intervention components and implementation strategies [59]. To operationalize processes within PRISM’s Adoption, Implementation, and Maintenance domains, we will use Normalization Process Theory (NPT) to guide qualitative data collection [39, 40]. NPT complements PRISM and considers the intervention itself, how staff understand the intervention, attitudes that develop around the intervention, and how it fits into existing roles, systems, and norms. We will use qualitative data to investigate how these processes and constructs shaped implementation and sustainment outcomes.

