#### Analysis plan, aim 2 (Implementation Strategy Effectiveness)

The primary outcome for Aim 2 is the proportion of sites that achieve ≥ 80% Reach. As in Aim 1, we will first describe site characteristics by implementation strategy bundle (standard vs. enhanced) and baseline proportions of screening and assessment. We will also fit mixed effects logistic regression models where the unit of analysis is the site, accounting for the longitudinal (repeated measures) design and for covariates such as level of champion engagement. Our primary interest is effectiveness of the standard vs. enhanced approach. Inference will be determined using odds ratios and 95% CIs and/or p-values. A similar strategy will be employed for secondary outcomes. We will compare recipient perspectives on the standard vs. enhanced approach using methods as in Aim 1 and triangulate qualitative and quantitative data on effectiveness of strategy bundles [65].

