This project also faces important challenges. One of the most notable is the high level of staff burden and burnout in U.S. primary care settings, related to both time limitations and the growing number of electronic screening tools. Although the current project is intended to reduce burden by streamlining existing screening tools, its focus on screening may still pose a barrier to site recruitment. Ongoing VA efforts to develop electronic screening tools that can be completed by patients or caregivers before an in-person visit may provide a promising alternative platform to disseminate the intervention, which we will explore in our pre-implementation adaptations. Participant burden related to completing evaluation measures (e.g., discussion forums, surveys) may also be an issue. To minimize burden, we have selected brief survey instruments and will use existing data when possible. We will also pilot the survey during Pre-Implementation and reduce its length and/or the frequency of data collection if needed. Based on staff preferences, we may also limit the number of synchronous data collection instances and substitute e-mail or Teams communications. Variability in champion engagement is also possible. We include plans to prepare and engage champions; will measure champion engagement using the fidelity checklist, CSAT, and periodic reflections; and will account for engagement in our analyses. It is also possible that Reach may be lower or higher than expected. If Reach is lower than expected, we will have sufficient capacity to deliver enhanced strategies at all 8 sites. If Reach is higher than expected, this information will help to inform the program design and resources needed for next-stage national implementation of the intervention. Finally, the roll-out of the Electronic Health Record Modernization (EHRM) within VA, which began in 2017, is an important consideration. We will work closely with our operational partners to develop electronic tools for sites that have migrated to the new Federal electronic health record (FEHR), and we will use FEHR data elements to capture outcomes.

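### The Aim 2 comparison adjusts for champion engagement without limiting it to a pre-randomisation value; if the assigned strategy affects engagement, the odds ratio is not the bundle's total effect

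*Protocol article*

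**What the plan says.** The Aim 2 analysis plan first describes sites by bundle. It then specifies mixed effects logistic models with the site as unit of analysis, "accounting for the longitudinal (repeated measures) design and for covariates such as level of champion engagement". The target of those models follows directly: "Our primary interest is effectiveness of the standard vs. enhanced approach". Champion engagement is the only covariate named there.

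The Discussion, on variability between champions, says the team "will measure champion engagement using the fidelity checklist, CSAT, and periodic reflections; and will account for engagement in our analyses".

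Randomisation is described under Period 1. Sites below 80% Reach after a 3-month run-in on the standard bundle are randomised 1:1. About 4 sites are expected to fall in this group.

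The standard bundle gives champions a defined part in audit and feedback: "Champions will receive monthly audit and feedback reports and will be responsible for sharing findings with other clinicians at their site". The enhanced bundle is the standard one "plus clinician-level audit and feedback for participating LVNs and PCPs instead of site-level audit and feedback".

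**The concern.** Adjusting a randomised comparison for a prognostic factor fixed before allocation is sound. Adjusting for something that allocation may have changed is different, because the coefficient for strategy then answers another question: what the strategy does with engagement held constant. If part of the benefit of clinician-level feedback comes through more active champions, that part drops out. If direct feedback makes the champions' relay role less important, the adjustment can push the other way.

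At stake is the estimate meant to tell the health system whether the enhanced bundle is worth deploying. That decision needs the total effect. The plan names this covariate without saying when it is measured, so an analyst following the text could use a post-randomisation value in the main Aim 2 model.

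**Working it through.** The article gives no effect size, power or sample size for Aim 2, so there is no stated figure to reproduce. Its one power calculation belongs to Aim 3. The check is mainly a reading of passages against each other.

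**1. When is engagement measured?** The Discussion names three instruments and gives no time points. Their uses elsewhere are:

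- *Fidelity checklist.* Aim 1: "Fidelity to intervention core components will be assessed to determine if core components were implemented as intended". Table 2 lists fidelity under Implementation.
- *CSAT short form.* Aim 1 uses it for clinician capacity for implementation and sustainment. Table 2 lists it under Maintenance.
- *Periodic reflections.* Aim 1: "Recipient experience will be assessed using periodic reflections for champions, interviews for leadership, veterans, and family caregivers, and surveys for clinicians".

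All three mainly describe what happens once delivery is under way. Delivery begins with the run-in, before randomisation, so a pre-randomisation value is possible. The text does not require one.

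**2. Could the strategy change engagement?** Champions receive the audit reports and pass on the findings. The enhanced bundle changes that component: the Implementation Team e-mails feedback directly to nurses and primary care providers. The enhanced-bundle section says site leadership keeps receiving system-level reports and does not mention champions in that sentence. Allocation therefore touches a task that champions perform. This makes an effect on engagement plausible; no passage states one.

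**3. Does the longitudinal design matter?** In Period 2 the strategy depends on earlier allocation and, for sites first assigned to standard, on Reach. A period-specific engagement value could therefore reflect both earlier strategy and earlier outcome.

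**4. Mechanism, with assumed coefficients.** None of these numbers comes from the documents. Let T be strategy, M engagement in SD units and Y the outcome:

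- M = a·T + standard normal noise
- logit P(Y = 1) = −0.2 + 0.8·T + 0.7·M

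The simulation used 400,000 independent records per scenario, with no clustering and no shared cause of M and Y. Odds ratios for enhanced vs standard:

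| a (SD) | Without M (total effect) | With M |
|---|---|---|
| 0 | 2.07 | 2.23 |
| 0.3 | 2.52 | 2.26 |
| 0.6 | 2.98 | 2.21 |
| 1.0 | 3.86 | 2.20 |

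With M in the model the odds ratio stays near exp(0.8) = 2.23 whatever the value of a, so the part acting through engagement is lost. At a = 0 nothing is removed; the gap between 2.07 and 2.23 is non-collapsibility of the odds ratio.

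**5. Direction.** On the log-odds scale the total is roughly 0.8 + 0.7·a. With a = −0.6 this is 0.8 − 0.42 = 0.38, and exp(0.38) = 1.46, while the adjusted odds ratio would still be about 2.23. Adjustment would then overstate the total effect. The sum is approximate because it ignores non-collapsibility: at a = +0.6 it gives exp(1.22) = 3.39 against 2.98 simulated. If the strategy affects engagement and an unmeasured factor such as staffing drives both engagement and Reach, conditioning on engagement adds a further bias of either sign.

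**The case against.** The strongest reply is that the timing and the causal path are both inferred. Champions are identified in the Pre-Implementation phase and work through a 3-month run-in before any site is randomised, so being measured during implementation is not the same as being measured after randomisation. Champions are in both bundles, and the added e-mails go directly from the Implementation Team to clinicians. The Discussion presents engagement as variability between champions, which reads like a prognostic nuisance factor. The wording of the Aim 2 plan marks the covariate as an example, and a condensed article may leave the measurement window to an analysis plan. Nothing excludes an unadjusted comparison as well.

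Much of this stands, and it limits the claim. A reader might infer any of the following, and the documents do not support them:

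- **The adjustment does remove part of the effect.** This holds only if the strategy changes engagement and the value used is post-randomisation. Neither is stated.
- **The bias is toward the null by a known amount.** Any odds ratio built from an assumed mediated share only restates that share, and the sign is not fixed.
- **The covariate cuts residual degrees of freedom from 2 to 1, raising the 95% t multiplier from 4.30 to 12.71.** That describes one cross-sectional comparison of four site means. The plan specifies a repeated-measures mixed logistic model in which strategy can change within a site. Four sites is only an expectation, and the Discussion allows for enhanced strategies at all 8. Having few sites is a separate problem.

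The reply does not remove the point itself. The covariate is named in the article, in the model meant to compare the strategies. The Discussion repeats the commitment, and its instruments lean towards delivery and sustainment. Restricting the covariate corrects a stated choice; it does not ask for missing detail.

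**Conclusion.** The point holds in conditional form. As written, the plan permits the Aim 2 strategy effect to be adjusted for engagement measured after randomisation. If the assigned strategy influences engagement, the resulting odds ratio is not the total effect of the enhanced bundle and may be too small or too large.

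The conclusion rests on two inferences: that the named instruments would supply post-randomisation values, and that changing audit and feedback can change what champions do. Both are reasonable from the text, and neither is established by it. The size cannot be computed from the documents; the simulated odds ratios show only the mechanism. Confidence is moderate. This is a cheap improvement.

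**What to change.** In the Aim 2 analysis plan, state that the primary standard vs enhanced comparison does not adjust for anything measured after randomisation. If covariates are used, limit them to information recorded by the end of the run-in, such as run-in Reach or a run-in engagement value, and only as far as the small number of sites allows. Assign engagement measured after randomisation to a separate analysis labelled exploratory or mediation. Bring the Discussion sentence on accounting for engagement into line.

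The cost is wording only: the same engagement data are collected and reported. The small downside is that differences in engagement arising after randomisation are no longer adjusted for in the primary model. The exploratory analysis can still describe them.

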#### Analysis plan, aim 3 (Clinical Effectiveness)

The primary outcome is the proportion of veterans with identified functional impairment(s) who receive appropriate referrals. As in Aim 1, the primary inference for effectiveness (standard vs. enhanced approach) is based on odds ratios and 95% CIs and/or p-values from logistic mixed effects models.

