**Fig. 2 Fig2:**
[figure not shown]
Flow Diagram for Adaptive Cluster-Randomized Controlled Trial. The figure shows the sequence of the four implementation periods, randomization, and cross-over allocation

In keeping with our operational partners’ interest in developing proactive approaches to identify high-risk veterans and intervene to prevent or delay functional impairment and associated acute care utilization, we will test the association of clinic-collected functional status measures with automated EHR-based frailty measures. Because frailty typically develops before functional impairment and may be a promising target for intervention [44–47], these findings will clarify how the two approaches might complement and inform one another.

Based on Primary Care and Office of Nursing Services capacity and input, we will implement the intervention in two waves, with 8 sites total. Sites may range in size depending on organizational capacity (e.g., a full community-based clinic or several primary care teams within a larger site). For both waves, we will cluster at the site level. Each site will move through three phases: Pre-Implementation, Implementation, and Sustainment (Fig. 3) [48].

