### Analysis

#### Analysis Plan, Aim 1 (Implementation Outcomes)

We will use descriptive statistics to examine patient- and site-level baseline measures, including outcome measures. For the primary outcome of Reach (0–100%), we will fit three-level mixed effects linear regression models that properly account for the longitudinal design and clustering of patients within sites. Our primary interest is whether baseline characteristics are associated with increased Reach. Inference will be determined using odds ratios and 95% confidence intervals (CIs) and/or *p*-values. A similar strategy will be employed for each secondary outcome.

To analyze Aim 1 qualitative data, we will use rapid analysis methods developed for implementation research that will allow us to use these data in real time to inform implementation strategies [70, 71]. The evaluation team will first develop summary templates with sections corresponding to each PRISM domain and NPT construct. Following each data collection instance, we will summarize key points in the appropriate section of the template; illustrative quotations will be included in summaries. A second team member will review the primary data source and summary for accuracy. We will use matrix analysis to synthesize template data, a method of displaying data to identify relationships between and across units of analysis [70]. Matrices will be organized by site to compare outcomes across sites and type of pre-implementation approach to measurement. Team members will meet regularly to discuss results.

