#### Missing data and power analysis

For each aim, when missing data exceeds 5% (for outcomes and/or model covariates), in addition to complete case analysis, we will implement and incorporate appropriate missing data methods (e.g., multiple imputation) within each aim’s analytical approach.

Power analysis for the primary clinical effectiveness aim of proportion of veterans receiving appropriate referrals shows that with a moderate effect size of 0.40, α = 0.05, and a design effect of 4.4 to adjust for clustered nature of our data, 80% power can be achieved with a sample of 730 participants. Given the large available sample size (estimated > 5,000 veterans from 8 sites), we have > 80% power to detect a significant difference in our primary clinical effectiveness outcome of proportion of Veterans receiving appropriate referrals.

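### The Aim 3 strategy comparison rests on about 4 randomised sites (8 at most), but its logistic mixed model has no stated few-cluster method; ordinary large-sample inference on the between-site comparison would far exceed 5% type I error

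*Protocol article*

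**What the plan says.** - **Analysis plan, aim 3:** "the primary inference for effectiveness (standard vs. enhanced approach) is based on odds ratios and 95% CIs and/or p-values from logistic mixed effects models". The outcome is measured on individual veterans with identified impairment. The section refers back to Aim 1, whose models account for the longitudinal design and for patients clustered in sites. Neither section names the test statistic, the degrees of freedom or a small-sample method.
- **Period 1:** for sites below 80% Reach, "we will randomize 1:1 by site to 3 additional months of standard vs. enhanced implementation". On numbers, "we anticipate that half of included sites" (n = 4) will need the enhanced bundle.
- **Overview of study design:** "For both waves, we will cluster at the site level".
- **Discussion:** if Reach is low, "we will have sufficient capacity to deliver enhanced strategies at all 8 sites". Eight is therefore the ceiling.
- **Missing data and power analysis:** effect size 0.40, α = 0.05 and "a design effect of 4.4 to adjust for clustered nature of our data" are said to give 80% power with 730 participants. Power above 80% is then claimed because more than 5,000 veterans are available from 8 sites.
- **Period 2:** sites randomised to standard that are still below 80% Reach cross to enhanced. Sites randomised to enhanced return to standard whatever their response.

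**The concern.** Veterans supply the outcomes, but only sites carry the randomised contrast. With 2 vs 2 sites there are 2 between-site degrees of freedom, and with 4 vs 4 there are 6. Large-sample Wald or likelihood-ratio inference treats the between-site variance as well estimated, although it comes from 4 to 8 sites. When the estimate falls to about zero, the model treats veterans as independent. The test then asks whether the two groups of sites differ at all, not whether they differ by more than sites ordinarily do.

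The power section points the same way. It inflates for clustering once, through the design effect, and then cites the pool of veterans across all 8 sites. It makes no allowance for how few sites are randomised.

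This is the primary effectiveness comparison of the two strategies, and the Background says the initiative is meant to inform national roll-out. A chance difference between a handful of sites could be reported as a strategy effect.

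**Working it through.** **1. The plan's own figure.** Per-arm n = 2(z₁₋α + z₀.₈)²/0.40², with α/2 in place of α for a two-sided test.
- Two-sided: 2(1.96 + 0.84)²/0.16 → 99 per arm; 99 × 2 × 4.4 = 871.
- One-sided: 78 per arm; 78 × 2 × 4.4 = 686.

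Neither gives 730. Working back, 730/4.4 = 166, or 83 per arm, which has 73% two-sided power by the normal approximation. The steps below do not depend on this mismatch.

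**2. Inputs for the type I error.**
- Randomised sites: 4 (2 vs 2) expected, 8 (4 vs 4) at most (Period 1; Discussion).
- Design effect 4.4 (power section), so ICC = 3.4/(m − 1) for m veterans per site.
- m is not given and is assumed. Examples: 730/8 = 91. Using the Background's impairment share, 459,000/2.8 million = 16.4%, 5,000 × 0.164/8 ≈ 102. An upper extreme of 5,000/8 = 625 ignores the restriction to impaired veterans.
- Referral proportion under the null: 60%, assumed.

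**3. Check without simulation.** A cut-off of 1.96 applied to a statistic that really follows a t distribution rejects 18.9% of the time on 2 df and 9.8% on 6 df.

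**4. Simulation, no strategy effect.** Random-site-intercept logistic model fitted by maximum likelihood, one parallel between-site comparison, nominal 5%. There were 1,000 trials per setting for m = 91, 102 and 625 (Wald only), and 2,000 for the others. Two separate runs were made at m = 100.

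| m | ICC | 2 vs 2: Wald | 2 vs 2: LR | 4 vs 4: Wald | 4 vs 4: LR |
|---|---|---|---|---|---|
| 50 | 0.069 | 21.6% | 15.4% | 13.1% | 9.9% |
| 91 | 0.038 | 20.9% | – | 13.0% | – |
| 100 | 0.034 | 20.5%, 21.7% | 14.7%, 16.1% | 13.0%, 15.0% | 9.5%, 11.1% |
| 102 | 0.034 | 19.8% | – | 12.3% | – |
| 180 | 0.019 | 20.5% | 15.8% | 13.3% | 9.6% |
| 625 | 0.0054 | 22.1% | – | 13.6% | – |

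With 2 vs 2 sites the estimated site variance was about zero in 37-41% of data sets (m = 91, 102, 625).

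**5. Away from the design effect of 4.4.** At m = 100 and ICC 0.0054, Wald rejects 9.5% (4 sites) and 8.6% (8 sites). At m = 100 and ICC 0.10, it rejects 27% and 15%. Over all the inputs tried and both tests, the range is about 7-27%.

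**6. Longitudinal crossover layout** (run-in and Periods 1-3, site intercept, 1,000 trials per setting).
- No site-by-period variation: 4.5% with 4 or 8 sites.
- Site-by-period variation present (SD 0.2, assumed) but not modelled: about 8-16%.
- Site-by-period variation modelled, z cut-off used, analytic approximation: about 6-15%.

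**7. With between-site degrees of freedom.** A t-test on site-level log-odds rejects 4.9% (4 sites, 2 df) and 5.2% (8 sites, 6 df). For power at N = 730, the noncentrality is 0.40/√(4 × 4.4/730) = 2.58. That gives about 31% on 2 df and 58% on 6 df. A randomisation test cannot replace it at 4 sites: its smallest two-sided p is 2/6 = 0.33, against 2/70 = 0.029 with 4 vs 4.

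**The case against.** **The article names no test.** A reader might infer that the planned analysis itself rejects a true null 12-22% of the time. The text does not support that. A mixed model with a small-sample correction would satisfy the Aim 3 sentence as written, and an analysis plan that is not shown may specify one. This stands, and it makes the error rates conditional. It does not dispose of the point. The ordinary reading of the stated model is large-sample inference, the likelihood-ratio test is also well above 5%, and the power section reasons from veterans without regard to between-site degrees of freedom.

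**The model is longitudinal.** Aim 3 refers back to Aim 1, Table 3 lists referrals in several periods, and there is a crossover. Within-site information could bring the error close to 5%. This stands only if sites do not vary by period. That contrast is also not purely randomised, because crossing from standard to enhanced in Period 2 depends on response.

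**Inputs are assumed.** The 60% proportion and the cluster sizes are not in the document, which is why the 7-27% range is given.

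**Other inferences that go too far.** A reader might conclude that the 95% interval covers only about 80%. That applies to 2 vs 2 sites; the 8-site error rates imply about 85-88%. A reader might extend the point to Aim 1, but that section describes a three-level linear model whose baseline characteristics include patient-level ones, and no calculation was made for it. Nor can it be said that the faulty fit would go unnoticed: a site variance of about zero shows in the output.

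**Conclusion.** The point holds conditionally. The primary Aim 3 contrast has about 2 between-site degrees of freedom (6 at most), and the article ties its interval and/or p-value to a logistic mixed model without a few-cluster method. With large-sample inference on the between-site comparison at the stated design effect, type I error is about 20-22% (Wald) or 15-16% (likelihood ratio) with 4 sites, and about 12-15% or 9-11% with 8. This rests on the assumed referral proportion and cluster sizes. A crossover model is near 5% only without site-by-period variation, and about 6-16% otherwise. The remedy is a change of wording, so the plan should be amended before the strategy comparison is analysed.

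**What to change.** Add to Analysis plan, aim 3, for example:

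> The test and 95% CI for standard vs enhanced will use between-site degrees of freedom. We will use either a logistic mixed model with a small-sample degrees-of-freedom correction that includes site and, where several periods are analysed, site-by-period variation, or a t-based analysis of site-level log-odds (critical value 4.30 on 2 df with 4 sites, 2.45 on 6 df with 8). No claim of significance will rest on the uncorrected model.

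Choose one of the two methods in advance. In the power section, restate the 80% figure on the same basis: at 730 participants, effect size 0.40 and design effect 4.4, power is about 31% with 4 randomised sites and 58% with 8.

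The change needs no new data. Its cost is wider intervals, from the critical value alone about 4.30/1.96 = 2.2 times with 4 sites and 2.45/1.96 = 1.25 times with 8, and the lower power shown. A single-period site-level t-test also gives up the longitudinal information, which is a reason to prefer the corrected mixed model if it can be fitted reliably with so few sites.
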